## Abstract

**Background:**

There is evidence of an association between alcohol use and offending behaviour and around a quarter of police time is spent on alcohol-related incidents. Police custody, therefore, provides an important opportunity to intervene. This pilot trial aims to investigate whether a definitive evaluation of screening and brief interventions aimed at reducing risky drinking in arrestees is acceptable and feasible in the custody suite setting.

**Methods:**

Screening will be carried out by trained detention officers or drug and alcohol workers in four police forces across two geographical areas (North East and South West England). Detention officers (or drug and alcohol workers) will be cluster randomised to one of three conditions: screening only (control group), screening followed immediately by 10 min of manualised brief structured advice delivered by the individual responsible for screening (intervention 1) or screening followed by 10 min of manualised brief structured advice delivered by the individual responsible for screening plus the offer of a subsequent 20-min session of behaviour change counselling delivered by a trained alcohol health worker (intervention 2). Participants will be arrestees aged 18+ who screen positive on the Alcohol Use Disorders Identification Test. Participants will be followed up at 6 and 12 months post-intervention. An embedded qualitative process evaluation will explore acceptability of alcohol screening and brief intervention to staff and arrestees as well as facilitators and barriers to the delivery of such approaches in this setting.

**Results:**

Recruitment is currently underway and due to end May 2015.

**Conclusion:**

Results from this pilot trial will determine if a definitive evaluation is possible in the future and will provide stakeholder input to its design.

**Trial registration:**

Reference number: ISRCTN89291046.

## Background

There is plentiful evidence of an association between alcohol use and offending behaviour [1-3]; however, the precise relationship is complex [4,5] due to an intricate interplay between drinking patterns, the amount of alcohol consumed and individual and contextual factors [6]. Alcohol has been found to be a factor in half of all violent crimes (defined as assaults, robbery and snatch thefts where the victim considered the perpetrator to be ‘under the influence’ of alcohol) [7]. In England and Wales, alcohol-related crime is estimated to cost society £11 billion per annum (2010–2011 costs) [8]. Moreover, around a quarter of police time is spent on alcohol-related incidents [9]. Recent research from the North East of England showed that 66% of adult offenders in probation and the prison system [10] and 59% of arrestees in a police custody setting [11] were hazardous, harmful or dependent drinkers. In both studies, screening for problematic drinking was carried out using the Alcohol Use Disorders Identification Test (AUDIT) which, at a cut-off point of 8+ (score range 0–40), has a sensitivity and specificity of 92 and 94% at identifying hazardous, harmful or dependent drinking [12]. Thus, heavy drinking is both a public health problem and a major burden on the criminal justice system.

Despite a wealth of evidence supporting brief alcohol intervention at reducing heavy drinking in health services [13-15], there has been relatively little research in the criminal justice sector. A recent quasi-experimental study in eight police custody settings in England found reduced alcohol consumption amongst arrestees who received a brief intervention; however, those in the intervention group were also statistically more likely to be re-arrested by 6 months post-intervention [16], although the comparison was a retrospective group of arrestees. In addition, just 34% of participants were followed up at 12 months which limits the generalisability of these findings [16]. An even lower follow-up rate of 20% was achieved in a Scottish pilot trial in community-based criminal justice settings [17]. Brief alcohol intervention in a magistrate court setting has resulted in lower levels of injury at 12 months compared to controls [18]. Finally, a recent trial based in probation (conducted as part of the SIPS programme [19]) included over 500 offenders and found reduced drinking in all three conditions (an additive combination of feedback following screening plus a leaflet-based control, 10-min structured brief advice and 20 min of behaviour change counselling) at 6 and 12-month follow-up [19]. Despite this lack of between-group differences, those in the brief advice (36%) or counselling (38%) groups were less likely to reoffend than controls (50%) in the year following brief intervention [19]. Thus, the criminal justice setting appears to be an important opportunity for alcohol intervention work, and relevant outcomes in this context should include both alcohol consumption and offending measures.

Only a proportion of individuals who are in contact with the criminal justice system are eventually managed by probation or prison services. Many arrestees only receive a caution due to ‘minor’ offences, and in other cases, there may not be sufficient evidence to proceed to a court case and/or trial. Thus, the police custody suite setting provides an important opportunity to target individuals who may be involved in alcohol-related disorder or have underlying alcohol problems but who otherwise do not have further engagement with criminal justice services. Moreover, the police setting provides an opportunity to access and intervene with a group that is perceived to be ‘hard to reach’ in public health work, that is, (often young) males who are typically socially deprived individuals and who tend not to present to health services [20].

Key barriers to carrying out alcohol research in this setting include the busyness of custody settings, time constraints for police officers and acceptability of interventions to arrestees. However, a recent mixed-method study of screening and brief alcohol interventions in a policing context provided some evidence for the feasibility of a controlled trial [11]. Screening and brief alcohol interventions were delivered for 3 months by detention officers, during finger-printing procedures, and this input appeared to be acceptable to the majority of arrestees since 77% agreed to be screened and 98% of those screening positive consented to brief alcohol intervention [11]. Nonetheless, whilst all detention officers in one police station were successfully trained to deliver study interventions, they reported mixed views about the experience with just half the officers expressing enthusiasm for the role of delivering brief interventions in this setting [11]. Additional exploratory work by Coulton et al. reported that the majority of English offenders (74%) in police, prison and probation settings did not feel coerced into participating in screening and brief intervention activity [21]. In one sub-urban area of France, forensic physicians, described as addiction specialists, reported high rates of substance use in the police custody setting and concluded that intervention delivery was feasible because arrestees seemed responsive to brief intervention input [22]. The perspectives of the arrestees were not reported. Consequently, it is necessary to establish views from both arrestees and routine police staff about the acceptability of screening and brief alcohol interventions in this setting. In addition, work in this field needs to be scaled up to a larger number of police stations and to a wider geographical area to establish the grounds for a definitive multi-site trial.

The MRC has presented a framework for the development and evaluation of complex interventions [23]. This present work represents the development and piloting phases of this framework. Consequently, we propose a pilot feasibility trial, including a specified comparator condition, in two areas of England involving multiple police stations.

## Methods/design

### Setting

Nine custody suite sites across four police forces and two geographical areas (North East and South West England) will be recruited into the study. Three police forces will be situated in the North East and one in the South West.

### Interventions

The three arms of the trial are additive and will include screening only (control group), brief advice (intervention 1) on the same occasion and brief lifestyle counselling (intervention 2) on a subsequent occasion.

#### Control condition

Arrestees will be screened using the AUDIT and assessed via the baseline questionnaire but they will not receive further alcohol-specific information or feedback on their screening responses.

#### Intervention 1—brief advice

Arrestees will be screened and assessed and then personalised feedback will be given on their screening score. This will then be followed by 10 min of structured brief advice about alcohol and its impact on health and offending behaviour. The brief intervention procedures will be fully manualised and based on the ‘How much is too much’ brief intervention programme (level 1), which was highlighted by the National Institute for Health and Clinical Excellence alcohol prevention guidance (PH24) as an evidence based brief alcohol intervention programme [24].

#### Intervention 2—brief lifestyle counselling

Arrestees will be screened and assessed and receive personalised feedback on their screening score. This will then be followed by 10 min of brief advice (as above) delivered by the individual carrying out the screening. Arrestees will then also be invited to a subsequent 20-min session of behaviour change counselling within 1 month and at an appropriate venue taking into consideration confidentiality, risk assessment and participant convenience and comfort. The counselling will be based on the ‘How much is too much’ programme (level 2) and include assessment of readiness to change (via numeric scales considering both the importance of, and confidence about, changing drinking behaviour), exploration of the pros and cons of changing and development of a practical and personalised six-step plan for changing drinking habits.

### Participants—interventionists

In two of three North East police forces, screening and brief advice will be carried out by detention officers. Detention officers have a distinct, civilian role within the custody suite setting and are responsible for an arrestee’s well-being; they have no role in interviewing or charging an arrestee. Therefore, these staff were previously identified as a suitable professional group to deliver the screening and brief interventions [11]. Furthermore, detention officers fingerprint arrestees immediately before they are released which represents an opportunity to screen and intervene at a time when the arrestee is least likely to be influenced by any alcohol consumption and has had time to reflect on the arrest incident [11]. However, early developmental work for this study indicated that the role of the detention officer had become privatised in some force areas, meaning that additional duties could not be added to their existing contracts. In these areas, drug and alcohol workers routinely support arrestees from a well-being perspective. Consequently, in the third North East site and in the South West, drug and alcohol workers carried out the screening and brief advice instead of detention officers. All staff will receive the same training in screening and brief advice procedures.

In all North East custody suites, a trained alcohol health worker will deliver the brief lifestyle counselling part of intervention 2. In the South West, this same individual will train the drug and alcohol workers to deliver the behaviour change counselling, meaning the same individual will deliver all parts of the intervention, unlike in the North East (see below).

### Participants—arrestees

Participants in this trial will be individuals aged 18 or above who are arrested (for any reason) and brought into the police custody suite to be either charged or released. Universal screening is more effective than targeting specific offences at identifying the full range of arrestees who could benefit from brief alcohol intervention because drinking level (or pattern) is not always known or recorded at the time of an offence. It is the subsequent screening outcome that will then determine if brief alcohol intervention should be delivered or not. The inclusion of hazardous and harmful, as well as dependent, drinking fits with the wider literature in this field [13-15] which indicates that the former groups often show greater responsiveness in terms of behaviour change than the latter. Thus, focusing on this spectrum of drinking has the greatest public health impact.

### Screening

Following informed verbal consent, screening will be carried out by participating detention officers or drug and alcohol workers using the 10-question Alcohol Use Disorders Identification Test (AUDIT) [12]. Based on alcohol consumption during the previous 6 months, participants who score 8+ on the AUDIT (score range 0–40) will be eligible for the trial and asked to provide informed written consent. A score of 8+ indicates hazardous (score of 8–15), harmful drinking (16–19) or probable dependent drinking (20+) [12]. It is anticipated that screening will take place during routine processing, whilst fingerprints and other details are taken in the North East or during assessment in the South West. Routine processing is the last procedure to take place before an arrestee leaves custody; this means arrestees have to be suitably fit to be released and will be sober when screening takes place.

#### Inclusion criteria

The first part of the screening process is an assessment of eligibility for the study and particularly whether or not an arrestee has the capacity to understand what they are being asked to consent to. Arrestees who are not deemed to be a danger to themselves or police staff will be eligible to take part in the trial if they can speak, read and write English and have a fixed abode and score 8 or more on the AUDIT questionnaire.

#### Exclusion criteria

An arrestee will not be eligible if they are grossly unwell (i.e. seeking medical attention), including having major psychiatric problems or alcohol withdrawal suggesting dependence which would require referral to specialist care. Major psychiatric problems include any serious mental health problems such as severe learning difficulties or schizophrenia. Any arrestee currently involved in other alcohol research will also be excluded from the study.

### Randomisation

The study will employ a cluster randomisation design in order to avoid contamination. Detention officers and/or drug and alcohol workers will be randomised to one of three trial arms using block randomization. The cluster randomisation involves randomising workers at each site to a trial arm, without allowance for whether the worker is a detention officer or a drug and alcohol worker. Allocation will be conducted by the study statistician. The randomisation sequence will be created in Stata 12 [25], using the macro *sxd1_2* (1) that permits block randomisation. The randomisation will be stratified by police custody site, with equal probabilities for the three arms and randomly generated varying block size. The trial statistician will write the Stata do file to perform the randomisation, but the randomisation sequence will be generated by another statistician not involved in the study to ensure concealment of allocation.

The arm to which each detention officer or drug and alcohol worker will be allocated will be written in a note placed within a sealed opaque envelope, with the officer’s name or unique ID number written on the outside. Neither the trial statistician nor the person delivering training to the officer will be aware of the allocation prior to the envelope being opened—in the officer’s presence—immediately before the training is delivered. Screening materials will be delivered in three separate, clearly marked boxes at each site. Each detention officer or drug and alcohol worker will be instructed to only take packs, in sequence, from the box that is labelled with the condition they have been allocated to. In each box, each individual pack will also be labelled in case of any movement due to the busy nature of the environment.

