### Sample size

This is a feasibility pilot trial and not an outcome evaluation; therefore, a formal power calculation is not required [32]. However, providing data that can inform the power calculation of a definitive trial is an important function of a pilot study; a minimum number of 30 participants per study arm (90 in total) at 12 months is recommended to estimate a parameter for this purpose [33] (Figure 1). Whilst this study involves cluster rather than individual randomisation, the relatively small average cluster size means that no major adjustment to the value cited by Lancaster et al. [33] is required. Specifically, assuming that around 30 detention officers or drug and alcohol workers are randomised and using an intra-cluster correlation coefficient of 0.04, the design effect would be 1 + [(90 / 30) −1] × 0.04 = 1.08.

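### Randomly varying block sizes fit poorly with about three workers per custody site: if sites hold 3 or 4 workers, about 2 to 5 of nine would lack an arm, which fixed blocks of 3 would avoid

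*Protocol article*

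**What the plan says.** The unit of randomisation is the worker: "The cluster randomisation involves randomising workers at each site to a trial arm" (Protocol article, Randomisation). The sequence is "stratified by police custody site, with equal probabilities for the three arms and randomly generated varying block size". The same section makes no separate allowance for whether a worker is a detention officer or a drug and alcohol worker. Each allocation goes into a sealed opaque envelope marked with the worker's name or ID, opened just before training. On supplies it says: "Screening materials will be delivered in three separate, clearly marked boxes at each site".

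The Setting section gives the number of strata: "Nine custody suite sites across four police forces and two geographical areas". The Sample size section gives the number of workers, as a planning figure: "assuming that around 30 detention officers or drug and alcohol workers are randomised". No block sizes and no number of workers per site are stated.

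**The concern.** A permuted block balances the arms only when it is filled. With about three workers in a stratum, a block of 3 is filled once, whereas a block of 6 or 9 stops part-way and may never reach one of the arms.

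Site stratification is the only balancing device in the plan. Through site it covers region, police force, who delivers screening and advice (detention officers in two North East forces, drug and alcohol workers elsewhere) and who delivers the counselling (a dedicated alcohol health worker in the North East, the same drug and alcohol workers in the South West). Where an arm is absent from a site, its recruitment, delivery and retention are not observed there, and arm is partly mixed with site and role. The success criteria are also set per condition (60 recruited and treated in each), so an arm that happens to receive few workers starts at a disadvantage unrelated to feasibility.

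Varying block size mainly protects against steering the next unit into a chosen arm when units enrol in sequence. Here the envelopes are already tied to named workers, so that protection buys little.

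**Working it through.** **The plan's own figure.** The design effect uses 30 workers and 90 participants at 12 months: 1 + (90/30 − 1) × 0.04 = 1.08. It reproduces. The plan gives no figure for arm balance by site.

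**Inputs.** Nine sites (Setting) and about 30 workers (Sample size): 30/9 = 3.33 per site. Assumptions, because the article does not state them: six sites of 3 workers and three of 4 (6 × 3 + 3 × 4 = 30); block sizes are multiples of 3, equally likely; each site starts a new block.

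**One site.** Let the first block have size 3k, with k places per arm. The first n workers are a random draw without replacement from it.

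- n = 3: P(an arm is missing) = 1 − k³/C(3k,3). Block 3: 0. Block 6: 1 − 8/20 = 0.600. Block 9: 1 − 27/84 = 0.679.
- n = 4: P(an arm is missing) = 3 × C(2k,4)/C(3k,4). Block 6: 3 × 1/15 = 0.200. Block 9: 3 × 15/126 = 0.357. If the first block is 3, all arms are already present: 0.

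**Nine sites.** Expected sites lacking an arm = 6 × (mean for n = 3) + 3 × (mean for n = 4).

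- Sizes 3, 6: 6 × 0.300 + 3 × 0.100 = 2.1
- Sizes 3, 6, 9: 6 × 0.426 + 3 × 0.186 = 3.1
- Sizes 6, 9: 6 × 0.639 + 3 × 0.279 = 4.7

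The chance that at least one site lacks an arm is one minus the product over sites; for sizes 3 and 6 it is 1 − 0.7⁶ × 0.9³ = 0.914.

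**Arm totals.** Combining the nine exact site distributions gives the distribution of workers per arm:

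| Rule | Sites lacking an arm (mean) | At least one such site | Some arm with 8 or fewer of 30 | Mean gap, largest to smallest arm |
|---|---|---|---|---|
| Fixed 3 | 0 | 0% | 0% | 1.7 |
| 3, 6 | 2.1 | 91% | 41.7% | 2.9 |
| 3, 6, 9 | 3.1 | 98% | 53.8% | 3.5 |
| 6, 9 | 4.7 | 99.9% | 64.5% | 4.2 |
| Simple, no strata | 6.3 | about 100% | 76.5% | 5.3 |

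**What fixed blocks of 3 leave behind.** Each site of 4 has one extra worker in a random arm. The three extras fall in three different arms with probability 6/27 = 22% (10, 10, 10). Otherwise, in 78%, some arm has 9 workers: 11, 10, 9 in 18/27 and 12, 9, 9 in 3/27.

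**Sensitivity to workers per site.**

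- Five per site: a block of 9 misses an arm with probability 3 × C(6,5)/C(9,5) = 18/126 = 0.143; a block of 6 cannot. Expected sites lacking an arm: 0 (sizes 3, 6), 9 × 0.143/3 = 0.43 (3, 6, 9), 9 × 0.143/2 = 0.64 (6, 9).
- Six per site: 3/84 = 0.036 for a block of 9, giving 0, 0.11 and 0.16.
- Uneven sites (1, 2, 2, 2, 3, 4, 4, 5, 7; total 30): 4.0 sites lack an arm under fixed blocks of 3, against 4.5 to 5.3 under the three varying sets; some arm has 8 or fewer workers in 38%, against 48% to 59%. The four sites with fewer than 3 workers lack an arm under any rule.

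**The case against.** **Unstated inputs.** The 30 workers are an assumption made for the design effect, the number per site is never given, and the Discussion speaks of larger centralised suites and of recruiting several staff in one suite. Block sizes are commonly left to the full protocol, so their absence is no fault. This stands as a limit on the size of the effect. It does not remove the point, because any varying set for three equal arms includes a block of at least 6.

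**Defeated stratification.** A reader might infer that stratification by site is defeated and that many sites lose an arm. The figures do not support that. Each varying rule examined did better than simple randomisation (2.1 to 4.7 sites against 6.3), and with sizes 3 and 6 it is about 2 sites of nine.

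**Concealment.** Neither the trial statistician nor the trainer is to know an allocation before the envelope is opened, and training may be one to one. With fixed blocks of 3, the last arm at a three-worker site can be inferred once two envelopes are open. This is a real but small cost: it cannot change a named worker's arm, though it could affect willingness to take part or how training is approached.

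**Recruitment target.** A reader might infer that a short arm will miss 60: at 180/30 = 6 participants per worker, 8 workers give 48. The plan sets no quota or cap per worker and treats recruits per worker as something to learn. By the same arithmetic fixed blocks of 3 leave some arm at 9 × 6 = 54 in 78% of randomisations. What stands is a larger dependence on chance, not a predicted failure.

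**Pilot status.** No hypothesis is tested and the key outcomes are descriptive, so no planned test is biased. The three boxes per site are logistics: they suggest all arms are expected at each site but do not promise it.

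**Conclusion.** The point holds as a weakness of a stated design choice. At the plan's own average of 3.3 workers per site, varying blocks give away balance that fixed blocks of 3 would keep. With sites of 3 or 4 workers, expect about 2 to 5 of nine sites without an arm, and a chance of about 42% to 65% that some arm has 8 or fewer of 30 workers, against zero for both. These figures rest on the assumed site sizes and block sizes. Sites lacking an arm become rare at 5 or 6 workers per site, and where sites are very uneven the advantage of fixed blocks shrinks without reversing. The consequence is less separation of arm from region, role and counselling model in the pilot's estimates, and per-condition recruitment that depends more on allocation chance.

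**What to change.** In the Randomisation section, replace the varying block size with permuted blocks of fixed size 3 within each custody site, generated by the independent statistician from the full list of named workers before any envelope is opened. Late joiners continue their site's sequence. Where a site has fewer than 3 workers, pool it with other sites of the same police force for stratification; no rule can put three arms in such a site, but pooling balances them at force level. Keep the sealed, named envelopes.

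The cost is one parameter in the Stata do-file, a stratum definition for small sites and one or two sentences of protocol text. Two downsides should be stated openly: the last arm in a block can be inferred, though not changed, and arms may still differ by up to three workers with the site sizes assumed here. Because the article reports that recruitment is under way, the change can apply only to workers not yet randomised. For those already allocated, tabulate workers by site and arm, and read the per-condition recruitment figures against that table.
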